				**Health system outcomes**
	**Health providers’ perceptions**			**Cost-effectiveness** (incremental costs and effects related to the intervention, related to maternal complications, intra-hospital perinatal deaths, Apgar score <7 and potentially avoidable caesarean sections)
	Access to the intervention during clinical work Participation rates during PartoMa seminars Perceptions of the intervention’s relevance, effects and limitations			
	**Health providers’ competencies**			
	Knowledge in management of intrapartum care Partograph skills			

##### C. Qualitative assessment

A mix of methods will be employed (participant observations, individual interviews, and focus group discussions (FGDs)) with a range of actors (birth attendants, hospital leadership, and women who have recently given birth). The aim is to investigate how participants experience, interpret, and engage with current maternity care, with a particular focus on respectful care and intrapartum decision-making in the case of prolonged labour and mode of birth. Further methodological details are presented separately [32].

##### D. Mixed-methods Analysis of Data Quality and Use

The quality and use of routine clinical data will be analysed through translational steps from clinical assessments to case file recordings, from case files to hospital registers, from registers to policy level and from policy level back to the frontline. This analysis will include quantitative and qualitative study findings mentioned above as well as further direct, structured observations and reviews of case files and registers.

#### II. Intervention co-creation

##### Co-creation process

The PartoMa pilot intervention from Zanzibar, including CPGs and training, will be modified and possibly elaborated, in accordance with pregnant women’s and birth attendants’ needs and circumstances in Dar es Salaam [49]. Co-creating and ensuring timely updating of CPGs may be highly resource-intensive for each single maternity unit in low-resource settings and it causes confusion if health providers are often shifted between facilities [22]. Therefore, and in line with demand by the regional medical officer in Dar es Salaam, the aim is to co-create only one version for all five sites.

We plan for a dynamic co-creation process lasting approximately six months, which might undergo adaptations on the way to reach the best possible, locally acceptable, simple, and realistic CPGs and training materials [49]. Sampling of co-creators will be opportunistic, with primary co-creator groups being nurse-midwives and medical doctors from the study sites. In addition, the intervention will be reviewed by hospital, district and regional health managers, by representatives from health colleges in Dar es Salaam and by an external panel of international experts in midwifery, obstetrics, and neonatology. The research team, including focal persons from the study sites, will facilitate and participate actively in the process. In particular, they will conduct and present situational analysis, summarize evidence, and provide scientific literature where needed (e.g. oxytocin augmentation in low-resource settings), synthesize inputs from co-creators and update the guidelines and training content accordingly.

A first draft of the modified CPGs and training content will be developed based on the situational analysis and initial FGDs with birth attendants (around five groups with 8–12 participants in each group, divided into professional backgrounds). Through a new round of FGDs and individual assessments of guidelines and training content, health providers will share their perspectives, which will inform further modifications. The iterative cycles of feedback from FGDs, intervention modifications, and reviews will be conducted until co-creators and reviewers are satisfied with the intervention and implementation plan (i.e. there are no more shared concerns regarding specific CPGs, training components, or graphic presentation, which might be dangerously (mis-)used in clinical work or lead to mistrust or neglect of the intervention) [26].

Notably, we aim for co-creators and birth attendants to acquire ownership through repeated discussions where openness and perceived control of the process are central. We hope that the actors will invest themselves in the process, as ownership may be strengthened by self-investment. Moreover, as reflected in the program theory (Figure 1), we hypothesize that co-creation leads to ownership, which will be a central driver of successful implementation and sustainability [49].

##### Analyses of co-creation

Three levels of analyses will be done of the co-creation process: *a*. core components of the intervention that ‘survive’ between settings and modifications needed will be identified and compared to both the Zanzibari PartoMa pilot intervention and international CPGs; *b*. whether and how co-creators influence the co-creation process and experience this will be ethnographically assessed through participatory observations and in-depth interviews; *c*. costs of the co-creation process will be recorded to inform the cost-effectiveness analysis of the PartoMa intervention.

#### III. Intervention implementation and evaluation

The overall implementation design will be a pragmatic stepped-wedged cluster-randomised trial with the five maternity units divided into three clusters receiving the intervention at cluster-level [50]. In a random order generated by R (R Core Team, 2017), maternity units will receive the intervention in three-month intervals. After enrolling in the third cluster, the intervention and evaluation will continue for additional nine months in all five sites (Figure 3).

**Figure 3. f0003:**
[figure not shown]
Overall implementation design for the pragmatic stepped-wedged cluster-randomized trial in five maternity units, divided into three clusters. Stars indicate when quarterly PartoMa seminars will be conducted in each facility. At the seminars, attendees’ perceptions and learning curves will be assessed. Quality of care (QoC) assessments through criterion-based audits and structured postpartum interviews with women will be conducted during baseline and the 7^th^ to 9^th^ intervention month at each maternity unit. Structured observations of infrastructure, equipment, data management and usage of the PartoMa guidelines will be conducted every three month. Birth outcome data, cost data and qualitative data will be collected continuously.

##### Evaluation of direct health outcomes

Our primary direct health outcomes are perinatal survival (stillbirths with positive foetal heart upon admission and pre-discharge neonatal mortality during the first seven days among inborn babies weighing ≥1000 g) and potentially avoidable CSs (by criterion-based case file review of care preceding surgery). Our secondary direct health outcomes include additional perinatal indicators (perinatal deaths divided into 1000–1999 g and ≥2000 g, first 24 hours pre-discharge neonatal mortality, Apgar score <7, admission to neonatal intensive care unit), maternal indicators (death, postpartum haemorrhage, uterine rupture, postpartum hysterectomy), and mode of birth (spontaneous vaginal birth, vacuum extraction, CS). In addition, background characteristics will be recorded for all women (age, parity, previous perinatal death, date and time of admission and birth, and birthweight). Sociodemographic indicators such as marital, economic, and educational status are not available in birth registries.

Birth outcomes and mode of birth will be prospectively measured from baseline and until nine months after the PartoMa intervention is implemented in the last facility. Thus, data collection will be ongoing for 18 months (Figure 3). Data will be gathered twice a week on each of the five study sites, primarily from the intrapartum birth register. Key indicators will be cross-checked with the antenatal, surgical, neonatal and postnatal wards registers and with the death certificate counter book. For each study site, data will be double entered every fifth week to ensure that the accuracy of data retrieval remains above 95%. Women referred to the study sites prior to birth from non-study health facilities will be included, but their clinical care prior to admission will not be possible to assess. When referrals occur from one to another study site, data will be recorded on where the woman gave birth. Babies referred postpartum for intensive care will be recorded at the facility where the woman gave birth (Table 1).

##### Evaluation of quality of care (QoC)

Quantitative assessments of potential changes in the QoC during birth are divided into provision and experience of care [51], with sample size calculations based on findings from the situational analysis.

For care provision, a criterion-based audit of case files will be conducted at each facility during three baseline months and the 7^th^-9^th^ implementation months (Figure 3, Table 1). This analysis is limited to intrapartum management preceding CSs, including the rate of potentially avoidable CSs, and intrapartum management of severe hypertensive disorders. These focus areas suit our preliminary assessments of data availability and accuracy in case files. Moreover, they represent a major challenge in reaching beyond the co-existence of TLTL and TMTS care to save lives [9]. Within the pre- and post-intervals at each study site, all case files will be assessed during the weekly data collection to retrieve case files of: i. women giving birth by CS; and ii. women suffering from severe hypertensive disorders (systolic BP ≥160 and/or diastolic BP ≥ 110 and/or eclampsia) (Figure 3, Table 1). Both the analysis of potentially avoidable CSs and the analysis of severe hypertensive disorders will be based on audit criteria, which were previously successfully applied in Tanzania [25,52,53]. Notably, indicators and methods for auditing case files might be further modified based on the final results of the situational analysis.

To assess potential changes in women’s experiences of care, women will be invited to respond anonymously to a validated, structured questionnaire through phone calls 2 to 4 weeks after birth. Compared to interviews before discharge where women have yet to reflect on their experiences, this timeframe has previously proven relevant in the Dar es Salaam context to ensure adequate reporting [54]. In each facility, the assessment will be conducted during the three baseline months and the 7^th^-9^th^ implementation months. The questionnaire is developed based on a qualitative participatory approach consisting of iterative rounds of feedback from local and international stakeholders [37,38,55]. The main focus areas are overall satisfaction with care and occurrences of disrespect and abuse [32].

In addition to this quantitative QoC evaluation, a broader qualitative investigation will be conducted as described below. Furthermore, to understand potential changes in the underlying structures within which care is provided and received, including usage of the PartoMa CPGs, all five facilities will be visited every third month throughout implementation and evaluation to retrieve data using a structured questionnaire (Table 1).

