**Table ut0001:** 

**Box 1** The PartoMa pilot intervention in Zanzibar, consisting of pocket booklets with locally co-created guidelines on common care during birth and associated quarterly recurring seminars, where the guidelines are practiced in groups passing through five stations. In Zanzibar’s tertiary hospital, a pre-post study suggested that the multifaceted PartoMa intervention appeared associated with a 33% decrease in stillbirths and halving in babies with low Apgar score. The intervention follows a ‘self-directed approach’ where use of the guidelines and participation in seminars are voluntary and based on inner motivation. At each seminar station, locally realistic case stories are discussed, based on partographs and both routine and emergency care during birth, respectful support, triage, and hands-on training are included. The Zanzibar PartoMa guidelines are available online (publichealth.ku.dk/partoma). *Photos by [name], [name] and [name]. All identifiable people have given their oral consent*.

Finally, a challenge arises if the success of the implementation is highly different across sites, which may leave the overall results of the stepped-wedged trial inconclusive. In this case, the theory-based, mixed-methods study design will allow us to conduct in-depth analyses focused on individual effects at hospital level, which can be compared across sites. This flexibility to assess intra- and inter-site variability is particularly important for addressing questions of transferability and scalability. In addition, while the current evaluation timeframe reflects our funding limitations, it may be argued that an evaluation time frame of nine to 15 months is insufficient for assessing potential long-term impact. If the intervention appears effective and continues, we aim to fundraising for additional post-exit evaluations, including in-depth exploration of long-term sustainability and potential further scale-up in Dar es Salaam and beyond.

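### The audit windows for potentially avoidable caesarean section, a primary outcome, never place a control site and an intervention site in the same calendar quarter, so the outcome has no concurrent randomised comparison

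*Protocol article*

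**What the plan says.** - **Status of the outcome.** Under Evaluation of direct health outcomes, the protocol article names two primary outcomes: perinatal survival and "potentially avoidable CSs (by criterion-based case file review of care preceding surgery".
- **Roll-out.** Section III describes a pragmatic stepped-wedge trial "with the five maternity units divided into three clusters receiving the intervention at cluster-level"; "maternity units will receive the intervention in three-month intervals". It continues: "After enrolling in the third cluster, the intervention and evaluation will continue for additional nine months in all five sites".
- **Length.** Evaluation of direct health outcomes: "Thus, data collection will be ongoing for 18 months". The limitations refer to an exposure range in the remark that "an evaluation time frame of nine to 15 months is insufficient for assessing potential long-term impact".
- **Audit calendar.** Evaluation of quality of care (QoC): "a criterion-based audit of case files will be conducted at each facility during three baseline months and the 7^th^-9^th^ implementation months". The Figure 3 caption agrees: the assessments "will be conducted during baseline and the 7^th^ to 9^th^ intervention month at each maternity unit". The women's experience questionnaire and the severe-hypertension audit use the same windows.
- **Continuous data.** Birth outcomes and mode of birth are collected throughout, mainly from the birth register. Classifying a CS as potentially avoidable needs the case-file audit.
- **Analysis.** Data analyses specifies mixed effects logistic regression, with time since implementation, seasonality and a list of covariates. It names no calendar-period term.

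**The concern.** A stepped-wedge design separates the intervention from background change because, in some calendar periods, sites already switched can be compared with sites still waiting. That requires the outcome to be measured in those periods. Here the only mixed periods are calendar months 4-9, and no intervention file is audited before month 10.

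The article itself names influences that move with time: COVID-19, staff often shifted between facilities, and competing interventions or unintended events. For this primary outcome their effect would enter the before-after difference. An analysis plan cannot repair this afterwards, because it cannot supply intervention files that were not audited while control sites still existed.

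**Working it through.** **1. Reproduce the calendar.** Three baseline months + (3 - 1) steps x 3 months + 9 months = 18 months, the stated total. Exposure runs from 9 to 9 + 2 x 3 = 15 months, the stated range. Five one-site steps would give 3 + 4 x 3 + 9 = 24 months, so that reading is excluded. Clusters start in months 4, 7 and 10.

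**2. Place the windows.** Implementation months 7-9 are start + 6 to start + 8.

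| Cluster | Start | Own preceding quarter | Post window | Gap, common baseline | Gap, own baseline |
|---|---|---|---|---|---|
| 1 | month 4 | 1-3 (Q1) | 10-12 (Q4) | 9 months | 9 months |
| 2 | month 7 | 4-6 (Q2) | 13-15 (Q5) | 12 months | 9 months |
| 3 | month 10 | 7-9 (Q3) | 16-18 (Q6) | 15 months | 9 months |

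The last control quarter is Q3 and the first post window is Q4. A one-quarter baseline can be chosen in 1 x 2 x 3 = 6 ways across the clusters. None overlaps a post window.

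**3. Estimability with calendar quarter.** Treatment status equals the indicator for Q4 or later. With site and quarter effects the design matrix has rank 8 with or without the treatment column, for the common baseline (5 + 4 - 1) and for own-quarter baselines (5 sites + 6 quarters - 3 unconnected blocks). The effect is not estimable on either reading.

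**4. What an assumed linear trend recovers.** Assume sites split 2/2/1 over clusters 1 to 3, and take the variance of one site-quarter as the unit. Each site's post-minus-pre difference then has variance 2.
- No time term: 2/5 = 0.40.
- Common baseline: gaps of 3, 4 and 5 quarters, mean (6 + 8 + 5)/5 = 3.8, sum of squares 2 x 0.64 + 2 x 0.04 + 1.44 = 2.8. Variance of the effect = 2 x (1/5 + 3.8²/2.8) = 10.7, and 10.7/0.40 is about 27. Ordering the sizes 2/1/2 gives 2 x (0.2 + 16/4) = 8.4; 1/2/2 gives 2 x (0.2 + 17.64/2.8) = 13.0.
- Own-quarter baselines: all gaps are 3 quarters, the sum of squares is 0, and the effect is not estimable with site fixed effects.

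**5. Seasonality adjustment.** With a common baseline only months 13-15 match the baseline season. With own-quarter baselines no post window matches its own baseline, and site fixed effects plus quarter-of-year terms alone already make the effect not estimable. A linear trend plus season is not estimable on either reading.

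**6. Size of a spurious effect.** The article gives no background trend, so this is an assumed range. With no true effect, a fall of 0.5%, 1% or 2% per month gives an apparent ratio of 0.94, 0.89 or 0.79 for a common baseline (mean gap (2 x 9 + 2 x 12 + 15)/5 = 11.4 months; for example 0.99^11.4 = 0.89). For own-quarter baselines the ratios are 0.96, 0.91 or 0.83 (9 months).

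**7. What spreading the audit recovers.** The present workload is 5 sites x 2 windows x 3 months = 30 site-months, which equals one month in each of six quarters at five sites. Rank rises from 10 to 11 when treatment is added. The information in the treatment column after removing site and quarter effects is 21 - 15.17 - 19 + 14.7 = 1.53, so the variance is 1/1.53 = 0.65 site-month units. A site-month holds a third of a site-quarter's files, so this is about 3 x 0.65 = 1.96 on the scale of step 4.

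**The case against.** **A reader might infer that the effect cannot be separated from trend by any model, or that the randomised roll-out contributes nothing.** That goes too far. With a common baseline, the staggered post windows allow a straight-line trend to be fitted alongside the effect (step 4). The estimate is weak and depends on the assumed shape, but it exists.

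**The article is partly open about this.** It describes the windows as pre and post intervals, separates the audits from continuously collected outcomes, and bases its power calculation on perinatal deaths only. No sentence promises a concurrent estimate for avoidable CS. This stands in part: some of the fault is labelling. Yet the outcome is called primary, the evaluation is described as stepped-wedge randomised, and the limitations do not mention the gap.

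**Adjustment is planned.** Covariates such as staffing, supplies, competing interventions and referral patterns may reduce confounding. They do not replace a calendar-period contrast, and seasonality adjustment fares as in step 5.

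**User fees might be added to the list of confounders.** The documents do not support that. Fees began in October 2019, before baseline, and no later change is stated, so site effects would absorb them.

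**There is partial mitigation.** Overall CS is recorded continuously, so it does have a concurrent comparison, but as a secondary outcome and without the avoidability judgement. The article also allows audit indicators and methods to change after the situational analysis; it does not say the windows will.

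**Months 7-9 were chosen to follow several quarterly seminars.** That is a fair reason to want the late window, and spreading the audit weakens it.

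**Conclusion.** The point holds as a statement about timing and estimability. No control and intervention site is audited in the same calendar quarter, and with calendar quarter in the model the effect on potentially avoidable CS is not estimable under any admissible baseline. This rests only on the article's own calendar; it does not depend on the unseen figure or on how sites are split into clusters. The factor of about 27 does depend on the 2/2/1 split and a linear trend, and the spurious ratios of 0.79 to 0.96 depend on assumed trends.

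The same applies to the severe-hypertension audit and the experience questionnaire. It would be wrong to extend it to the whole trial: perinatal survival, the outcome the trial is powered on, and overall mode of birth are collected continuously and keep their concurrent comparison.

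**What to change.** **Preferred.** Spread the same 30 site-months of audit and interviews over all six calendar quarters at every site, for example one month per quarter or a fixed random fraction of CS files per quarter, and include calendar quarter in the model. Spreading over the first four quarters only is less suitable, because clusters 2 and 3 would then never be audited in implementation months 7-9.

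**Cost.** The number of site-months is unchanged, but the article does not show that a longer audit calendar costs the same to run. Fewer files fall in implementation months 7-9, and early exposure months enter the estimate. Concurrent controls exist only in calendar months 4-9, so they cover at most 6 months of exposure.

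Precision rests on inputs the article does not give. Assuming 200 CS files per site-month, 40% avoidable and a constant effect, the SE of the log odds ratio is √(0.652/(200 x 0.4 x 0.6)) = 0.117 with sampling error only. With a site-by-quarter SD of 0.1 or 0.2 on the log-odds scale it is √(0.652 x (0.0208 + 0.01)) = 0.142 or √(0.652 x (0.0208 + 0.04)) = 0.199. These figures should be redone with situational-analysis data.

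**If the present windows are kept.** State explicitly that potentially avoidable CS, the hypertension audit and the experience questionnaire are non-randomised before-after comparisons, add this to the limitations, and do not report them as stepped-wedge randomised effects. This costs wording only, but leaves one primary outcome without randomised evidence.

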**Workload***(patient volume; numbers, composition and organization of providers; provider-to-labouring women ratios)* **Management /leadership structure** **Infrastructure and supplies***(physical organization of maternity units, essential medication, monitoring devices, birth equipment, disinfection facilities, personal protective equipment)* **Other ongoing interventions***(e.g. training, supervision, clinical practice guidelines, construction)* **Data quality***(registration of clinical assessments, maintenance and use)* **Referral systems**	**Clinical surveillance** Admission assessment *(history and physical assessment)* Partograph use Foetal wellbeing *(by foetal heart auscultation)* Labour progression *(by recordings of cervical dilatation and membranes)* Maternal vital signs *(blood pressure, pulse rate, temperature)*	**Intrapartum treatment** Caesarean section *(divided into medically indicated and potentially avoidable)* Prolonged labour *(incl. timely and safe use of artificial rupture membranes and oxytocin)* Severe hypertensive disorders *(incl. timely use of antihypertensives and magnesium sulphate)*	**Caring support** Communication *(incl. verbal and physical abuse)* Birth companionship and emotional support Respect and preservation of dignity *(e.g. privacy)* Pain relief Mobilization and birth position User fee structure	**Primary outcomes** Perinatal survival *(intra-hospital stillbirths, pre-discharge neonatal deaths within 7 days)* Potentially avoidable caesarean sections *(by assessment of care before caesarean section)* **Secondary outcomes** Perinatal outcomes *(perinatal deaths divided into 1000–1999 g and ≥2000 g, neonatal first 24 hours pre-discharge mortality, Apgar score <7 and <9, admissions to neonatal intensive care)* Maternal outcomes *(death, postpartum haemorrhage, perineal tear, uterine rupture, postpartum hysterectomy)* Mode of birth *(spontaneous vaginal birth, vacuum extraction, caesarean section)*

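### Primary outcome of potentially avoidable CS has no stated denominator; if it is a share of CSs, as the audit text suggests, the intervention may change the denominator and the share can mislead

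*Protocol article*

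**What the plan says.** Under Evaluation of direct health outcomes, the second primary outcome is given as "potentially avoidable CSs (by criterion-based case file review of care preceding surgery" and nothing more. The other primary outcome, perinatal survival, is given a population there: babies born in the facility above a birthweight limit, with a foetal heartbeat on admission required for stillbirths.

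Under Evaluation of quality of care (QoC), the audit runs "during three baseline months and the 7^th^-9^th^ implementation months" at each site. Its scope is: "This analysis is limited to intrapartum management preceding CSs, including the rate of potentially avoidable CSs, and intrapartum management of severe hypertensive disorders". For this outcome, "all case files will be assessed during the weekly data collection to retrieve case files of: i. women giving birth by CS". Table 1 describes CS as "divided into medically indicated and potentially avoidable".

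The secondary outcomes include "mode of birth (spontaneous vaginal birth, vacuum extraction, CS" as its last category. On data collection, "Birth outcomes and mode of birth will be prospectively measured from baseline" and continue to the end of the 18 months, mainly from the birth register.

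The Data analyses section assigns mixed effects logistic regression to the quality-of-care indicators and to the birth outcomes. It does not say which women form the population at risk for avoidable CS.

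**The concern.** The clinical question is whether fewer women have a CS that better care could have avoided. That is a risk among women giving birth. A share among CSs answers a different question, namely how the CSs that took place divide into two classes.

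The number of CSs is settled after the intervention starts, and the intervention may change it. The protocol's Background links unnecessary CS to poor surveillance and care during birth, and the quality-of-care section describes care that is both too late and too much. On that rationale avoidable and indicated CSs could both move, and not necessarily in the same direction. A share would then compare differently selected groups of women before and after, and would mix the two movements. With the denominator open, the same data can also yield two different results for one primary outcome.

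**Working it through.** **The plan's own figures.** The only power figure, 80% at an RR of 0.78, concerns perinatal deaths. Sample sizes for the audit outcomes are deferred to the situational analysis. No baseline share or target effect is given for avoidable CS, so there is no figure to reproduce.

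**Inputs.** The protocol gives neither a CS rate nor an avoidable share for the study sites. Assumed for illustration: a 25% CS rate and 40% of CSs avoidable. In 1,000 births this gives 250 CSs, of which 100 are avoidable (A) and 150 indicated (I). The shifts of 22% and 30% below are also assumed.

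**Two candidate measures.** Per birth: A / births. As a share: A / (A + I).

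| Scenario | A | I | CS rate | Share of CSs | RR, share | RR, per birth |
|---|---|---|---|---|---|---|
| Baseline | 100 | 150 | 25.0% | 0.400 | – | – |
| 1. Avoidable −30%, indicated unchanged | 70 | 150 | 22.0% | 70/220 = 0.318 | 0.80 | 0.70 |
| 2. Both −30% | 70 | 105 | 17.5% | 70/175 = 0.400 | 1.00 | 0.70 |
| 3. Avoidable unchanged, indicated +30% | 100 | 195 | 29.5% | 100/295 = 0.339 | 0.85 | 1.00 |
| 4. Avoidable −22%, indicated −30% | 78 | 105 | 18.3% | 78/183 = 0.426 | 1.07 | 0.78 |

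The share understates the reduction in scenario 1, misses it in scenario 2, suggests one that did not occur in scenario 3, and points the wrong way in scenario 4.

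**Sensitivity to the assumptions.** Let s be the baseline avoidable share, and let a and i be the factors by which avoidable and indicated CSs change. Then

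RR of share = a / (s·a + (1 − s)·i).

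The CS rate does not appear in this formula, so the assumed 25% does not matter. Varying s from 0.20 to 0.60:

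- Scenario 1: 0.70/(0.14 + 0.80) = 0.74 to 0.70/(0.42 + 0.40) = 0.85. The per-birth RR is 0.70 throughout.
- Scenario 2: 1.00 throughout, against 0.70 per birth.
- Scenario 3: 1/(0.20 + 1.04) = 0.81 to 1/(0.60 + 0.52) = 0.89, against 1.00 per birth.
- Scenario 4: 0.78/(0.156 + 0.56) = 1.09 to 0.78/(0.468 + 0.28) = 1.04, against 0.78 per birth.

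**Can the per-birth measure be computed from planned data?** Yes. A vaginal birth cannot be an avoidable CS, so only CS files need auditing and every other birth scores zero. The denominator comes from the register.

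**The case against.** A reader might infer that the protocol commits to a share among CSs. It does not. The sentence on scope limits which care is audited and does not name a denominator. Retrieving only CS files proves nothing either way, because a per-birth measure needs the same files. The regression is not restricted to audited files. A share is the more natural reading, but it remains an inference. Nor do the documents show that the intervention will change the number of CSs; they show only that it may.

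It can also be said that an article leaves analysis sets to the full protocol or the SAP, and that audit methods may still be modified after the situational analysis. This carries some weight. However, the population is part of what a primary outcome is, and this article supplies it for perinatal survival. The point is also more than a request for detail, since the reading that the text suggests is the weaker estimand.

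The secondary CS rate helps: the share multiplied by the CS rate in the same period gives the per-birth rate (scenario 2: 0.400 × 0.175 = 0.070). That recovers a point estimate. The test and interval for the primary outcome would still concern the share. The CS rate is also collected over 18 months, while the audit covers two three-month windows per site, so the two match only if the CS rate is restricted to those windows.

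A per-birth rate has a drawback of its own: changes in case mix and referral can shift it. The planned covariate adjustment, which includes maternal characteristics and referral patterns, already addresses this.

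**Conclusion.** The point holds in conditional form. The protocol states no denominator for one of its two primary outcomes, and its operational text points to a share among CSs. If that is the measure, it conditions on something the intervention may change. With an assumed 40% baseline share, a 30% fall in avoidable CSs per birth can appear as an RR of 0.80 or 1.00, and no fall at all can appear as 0.85. The direction of these distortions is the same for baseline shares from 20% to 60% and does not depend on the CS rate. The sizes rest on assumed shifts in the two classes and show what can happen, not what will. The change should be made before analysis, but it does not call the design or the data collection into question.

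**What to change.** 1. Define the primary measure as potentially avoidable CS (yes or no) among all women giving birth at the site in the same audit windows, with the denominator from the birth register. If the trial's labour population is preferred, so that pre-labour CSs do not enter, name that population instead and apply it to both numerator and denominator.
2. Report the share among audited CSs as a supporting process measure, next to the CS rate for the same windows.
3. If some CS files cannot be retrieved, report the number by site and period. Treat weighting of audited files up to the register count of CSs as a sensitivity analysis, and state its assumption that missing files resemble retrieved ones.

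The all-births version costs protocol wording only, since births and mode of birth are already to be recorded for all women. The per-birth rate is more exposed to case mix and referral, for which adjustment is already planned.
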